#### 2.1.2. Specialist SENSe Therapy Centers and SENSe CONNECT Protocol

Four specialist SENSe therapy centers have been set up to deliver SENSe therapy to stroke survivors across three states in Australia. The new specialist therapy centers are linked with healthcare networks and universities or research institutes. The SENSe therapy centers will permit delivery of therapy to stroke survivors living in the community. Therapy may be delivered at the center or in the client’s home.

Occupational therapists and physiotherapists skilled and credentialled in SENSe therapy will deliver SENSe therapy to stroke survivors across the specialist therapy centers, using a pragmatic, within-subject wait list design [42]. The wait list design will evaluate change in outcomes over a 6-week period of usual care not associated with SENSe therapy, compared to a 6-week period of SENSe therapy delivered by credentialled therapists. During the wait list phase, participants will receive usual care, which will be monitored. Upper-limb therapy will not be restricted for participants during the control wait list phase; rather, participants will receive ‘usual care’ conditions [44]. Consistent with an independent review and analysis of ‘usual care’ usually received in health services in Australia (based on national audit and knowledge-translation study), this will usually not involve specific sensory rehabilitation, such as SENSe therapy [44]. Participants may continue to receive usual care during the SENSe therapy intervention period. Our prior controlled clinical trials provide evidence that exposure to sensory stimuli alone and/or current usual care is not usually sufficient to affect clinically significant improvement in somatosensory function [34,36,37]. All services and usual care received will be monitored.

Stroke survivors attending specialist SENSe therapy centers will be assessed on four occasions: baseline (i.e., Assessment 1, A1); after 6 weeks of usual care (i.e., A2); after 6 weeks of SENSe therapy (i.e., A3); and at follow up, 12 weeks post A3 (i.e., A4). All participants attending SENSe therapy centers will receive SENSe therapy (10 sessions) over a 6-week period. Assessors for health outcomes of stroke survivors will be blinded to study design and timing of therapy delivery. Researchers and statisticians involved in the data analysis will also be blinded to study design and timing of therapy delivery.

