### 2.4. Outcomes

Access to evidence-based sensory rehabilitation: The primary outcome is the number of complete deliveries of SENSe therapy at the SENSe therapy center by therapists credentialled in SENSe therapy. A delivery will be counted as complete if it meets the criterion of at least 7 sessions delivered with a stroke survivor.

Stroke survivors: The primary outcome is change in arm somatosensory function, pre–post SENSe therapy, across three somatosensory domains, measured using standardized, quantitative somatosensory measures and a normalized summary impairment index calibrated to normed age-matched performance [34,45]. The index will be derived from scores on the Tactile Discrimination Test [46], Wrist Position Sense Test [47], and functional Tactile Object Recognition Test [48]. Each of these quantitative measures assesses the person’s ability to discriminate different somatosensations; i.e., texture discrimination, wrist joint proprioception, and haptic object recognition of the upper limb. Comparable ranges of impairment from just noticeable to extreme impairment defined for each measure enable the normalization of the three test scales for comparison in clinical and research settings [45].

The following secondary outcomes will also be assessed: client-rated performance and satisfaction of valued activities, using the Canadian Occupational Performance Measure (COPM) [49] and clinician-rated performance on the same valued activities using the Performance Quality Rating Scale for Somatosensation after Stroke [50]; arm use, using Motor Activity Log-14 [51]; and health-related quality of life, using the Assessment of Quality of Life (AQoL-6D) [52]. See Table 1 for the schedule of study outcomes.

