Effect of SENSe therapy: We will evaluate the therapeutic gain in arm somatosensory function for stroke survivors (primary outcome) during the SENSe therapy phase compared to that of the usual care phase by estimating the mean within-person difference between the two trends and the associated 95% confidence intervals. The magnitude of change in arm somatosensory function under the two conditions will be calculated as a standardized effect size and compared to the benchmark effect size obtained in the original SENSe RCT (comparable cohort) [34]. Statistical estimates of change will be reported with 95% confidence intervals, and the extent of overlap across studies in these estimates of change will be described. Confidence intervals for the difference between mean change scores from the present and benchmarked study [34] will also be obtained. The analysis design will include the SENSe therapy center as a variable, to evaluate its potential systematic effect. Individual participant characteristics that may impact magnitude of therapeutic gain, such as age and time post-stroke, will be explored. Improvement in secondary outcomes, i.e., clinician-rated performance in valued activities, arm use, and quality of life, will also be evaluated pre–post therapy. Depending on verification of the normal distribution assumption, either a t-distribution or a bootstrapping method will be used to obtain the confidence interval. Maintenance of the intervention effect will be evaluated at the 12-week follow up (A4).

Treatment fidelity and behavior change: High fidelity delivery will be defined as a score of 80% or higher on the SENSe treatment fidelity checklists [43]. Audit data from treatment sessions will be independently summarized for each SENSe therapy treatment program delivered. The number of therapy deliveries achieving high treatment fidelity will be summarized. Pre- and post-implementation questionnaires of therapist knowledge, confidence, and ability to deliver SENSe therapy will be summarized and response tendencies will be examined using contingency tables, McNemar’s test, and graphical representation.

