**Figure 2 healthcare-11-03080-f002:**
[figure not shown]
Images of SENSe therapy specialized equipment and activities used in training modules, including (**a**) discrimination of texture grids; (**b**) training of wrist proprioception using the box-like apparatus and protractor scales; (**c**) training of graded sets of everyday objects that vary in objects with varying diagnostic attributes such as crushability, shape, size, and weight; and (**d**) training in the context of self-chosen valued activities impacted by sensory loss.

**Table 1 healthcare-11-03080-t001:** Study Schedule of Assessments: SENSe CONNECT.

Outcome	Measure	A1 (Baseline)	A2 (6 Weeks Post A1)	A3 (6 Weeks Post A2)	A4 (12 Weeks Post A3)
*Survivor of Stroke*					
Arm somatosensory function	Tactile Discrimination Test (TDT)	X	X	X	X
	Wrist Position Sense Test (WPST)	X	X	X	X
	Functional Tactile Object Recognition Test (fTORT)	X	X	X	X
Performance of valued activities	Canadian Occupational Performance Measure (COPM) Performance Quality Rating Scale for Somatosensation after Stroke	X X	X X	X X	X X
Arm use	Motor Activity Log (MAL)-14 item version	X	X	X	X
Health-related quality of life	Australian Quality of Life (AQoL-6D)	X	X	X	X
Resource utilization	Resource Use and Productivity Questionnaire	X	X	X	X
Other	National Institute of Health Stroke Scale (NIHSS)	X			
	Modified Rankin Scale (mRS)	X			
	Montreal Cognitive Assessment (MoCA)	X			
	Jebsen Taylor Hand Function Test (JTHFT)	X			
*SENSe Therapist*					
Treatment fidelity	Customized Documentation Audit Checklist	Post delivery of SENSe therapy to each survivor of stroke.			
Practice behavior change	Pre–Post Implementation Questionnaires	Prior to first delivery of SENSe therapy and after delivery of therapy to 12th survivor of stroke, or last scheduled delivery for that therapist.			

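### Section 2.8 gives the secondary outcomes a pre–post evaluation and leaves client-rated COPM off the list, in conflict with the wait-list comparison, the declared outcomes and the assessment schedule

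*Protocol article*

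**What the plan says.** **Analysis (section 2.8, Effect of SENSe therapy).** The therapeutic gain on the primary outcome is evaluated "during the SENSe therapy phase compared to that of the usual care phase by estimating the mean within-person difference between the two trends". Later in the same paragraph: "Improvement in secondary outcomes, i.e., clinician-rated performance in valued activities, arm use, and quality of life, will also be evaluated pre–post therapy".

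**Design (section 2.1.2).** "The wait list design will evaluate change in outcomes over a 6-week period of usual care not associated with SENSe therapy", set against the same length of SENSe therapy. The word used is outcomes, with no restriction to the primary. The visits are "baseline (i.e., Assessment 1, A1); after 6 weeks of usual care (i.e., A2); after 6 weeks of SENSe therapy (i.e., A3"), with A4 twelve weeks after A3.

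**Outcomes (section 2.4).** The secondary outcomes begin with "client-rated performance and satisfaction of valued activities, using the Canadian Occupational Performance Measure (COPM"). The clinician-rated Performance Quality Rating Scale, MAL-14 and AQoL-6D follow. The primary outcome is worded: "The primary outcome is change in arm somatosensory function, pre–post SENSe therapy, across three somatosensory domains".

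**Schedule (Table 1).** COPM, the Performance Quality Rating Scale, the "Motor Activity Log (MAL)-14 item version" and AQoL-6D are each marked at all four assessments.

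**The concern.** One paragraph describes two kinds of analysis. The primary outcome is compared with each participant's own usual-care phase. The secondary outcomes are described by their change across therapy, and no comparator is named. An analyst following section 2.8 literally would report A3−A2 for valued activities, arm use and quality of life.

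That change mixes any therapy effect with whatever would have happened over six weeks anyway: recovery (eligibility sets no limit on time since stroke), continuing usual care, and familiarity with the tests. The run-in from A1 to A2 exists to measure this. Section 2.1.2 cites earlier trials in which usual care usually gave no clinically significant improvement, but it speaks of somatosensory function and not of the secondary measures.

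Aim 2 includes improvement in these outcomes, and aim 5 uses them for cost-effectiveness, where incremental results need a difference from usual care.

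Separately, the list in section 2.8 is introduced by i.e., so it reads as complete. A declared secondary outcome, client-rated COPM performance and satisfaction, then has no stated analysis, and how it is reported is left open.

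**Working it through.** **1. The texts side by side**

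| Item | 2.1.2 | 2.4 | Table 1 | 2.8 |
|---|---|---|---|---|
| Somatosensory function | covered by outcomes | primary, pre–post | A1–A4 | phase contrast |
| COPM performance, satisfaction | covered by outcomes | secondary | A1–A4 | not listed |
| Performance Quality Rating Scale | covered by outcomes | secondary | A1–A4 | pre–post |
| MAL-14 | covered by outcomes | secondary | A1–A4 | pre–post |
| AQoL-6D | covered by outcomes | secondary | A1–A4 | pre–post |

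The data for a phase contrast will exist for every row. Section 2.8 states one for the first row only.

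**2. The plan's own figure**

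The only sample-size figure for stroke survivors is n = 61 for a within-group d of 0.366 at power 0.8, and it concerns the primary outcome. A paired t-test, using the noncentral t with two-sided alpha 0.05 (assumed, as the article states none), gives power 0.803 at n = 61 and 0.796 at n = 60. The figure reproduces. The same calculation is used below. The article gives no effect size, SD or drift for any secondary outcome.

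**3. What background change does to a pre–post estimate**

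Let g be the mean change over six weeks without therapy, in SDs of the change score, and let the therapy effect be zero. The pre–post t statistic is noncentral t with n−1 degrees of freedom and noncentrality g√n. The chance that the 95% interval excludes zero is P(|T| > t(0.975, n−1)). The values of g are assumptions.

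| g | n = 72: g√n | chance | n = 192: g√n | chance |
|---|---|---|---|---|
| 0 | 0 | 5% | 0 | 5% |
| 0.1 | 0.1 × 8.485 = 0.85 | 13% | 0.1 × 13.856 = 1.39 | 28% |
| 0.2 | 0.2 × 8.485 = 1.70 | 39% | 0.2 × 13.856 = 2.77 | 79% |

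The problem grows with n, because the larger sample estimates the wrong quantity more precisely.

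**4. What the contrast costs**

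For (A3−A2) − (A2−A1), with equal SDs of the two changes and correlation r between them, the SE relative to a pre–post change is √(2 − 2r):

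- r = +0.5: √1, no increase.
- r = 0: √2.
- r = −0.5 (equal correlation among visits): √3.

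As an illustration, borrow d = 0.366 for a secondary pre–post change and assume no change under usual care. The contrast then has d = 0.366/√(2 − 2r):

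| r | d | n for 80% power | power, n = 72 | power, n = 192 |
|---|---|---|---|---|
| +0.5 | 0.366 | 61 | 0.87 | 0.999 |
| 0 | 0.259 | 120 | 0.58 | 0.95 |
| −0.5 | 0.211 | 178 | 0.42 | 0.83 |

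**The case against.** The strongest reply is that section 2.8 does not say what it seems to say. It states that secondary outcomes will also be evaluated pre–post. It does not say that they will be evaluated in no other way, or that the A1–A2 data are set aside. Section 2.1.2 applies the phase comparison to outcomes generally. Section 2.4 even words the primary outcome as a pre–post change, and that outcome is plainly compared with usual care. So pre–post cannot be taken to mean uncontrolled in this article. This stands: a reader might infer that the control data are discarded for the secondary outcomes, and the text does not support that. What it shows is an inconsistency that allows such an analysis.

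A reader might also infer that COPM has been dropped. It has not. It remains in section 2.4 and at every visit in Table 1, and its omission may be a drafting slip.

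Nor do all the secondary outcomes share the same exposure to expectation. Outcome assessors are to be blinded to design and timing, so the concern fits the self-reported COPM, MAL-14 and AQoL-6D better than the clinician-rated scale. Participants know when they are receiving therapy, so expectation would arise mainly between A2 and A3, and subtracting A1–A2 change does not remove it. The contrast answers time and repeat-testing drift, and only that.

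Finally, an article may leave detailed models to an analysis plan that is not shown. That would excuse silence. Here an analysis is stated, and it does not match the design section or the outcome list.

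**Conclusion.** The point holds as an inconsistency with consequences. Section 2.8 states a phase contrast explicitly for the primary outcome alone, gives the secondary outcomes a pre–post evaluation, and omits a declared secondary outcome from a list worded as complete. Sections 2.1.2 and 2.4 and Table 1 point the other way.

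If section 2.8 is followed literally, background change is credited to therapy. How much is unknown, because the documents report no usual-care change for these measures. The 13–28% and 39–79% figures rest on assumed drifts of 0.1 and 0.2 SD of change, equal in both phases, with no therapy effect and two-sided alpha 0.05. With zero drift the rate is the nominal 5%. These figures illustrate sensitivity and do not predict this trial's error rate.

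**What to change.** Amend the sentence in section 2.8 to say that every secondary outcome is analysed with the same within-person contrast as the primary outcome, (A3−A2) minus (A2−A1), with a 95% confidence interval, and that the pre–post change A3−A2 is shown descriptively. The outcomes to name are COPM performance, COPM satisfaction, the Performance Quality Rating Scale, MAL-14 and AQoL-6D. The wording in sections 2.1.2 and 2.4 should then agree with it.

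The change needs no new assessments, and the article reports that no results exist yet. The cost is precision: the SE is between unchanged and about √3 times that of a pre–post change for a correlation between the two changes from +0.5 to −0.5. At the lower end of recruitment some secondary contrasts may be imprecise, and the intervals should be reported as such.

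Add a sentence acknowledging that the contrast removes drift common to both phases but not expectation specific to the therapy phase, which matters most for the self-reported scales.

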Skill and experience of the therapist may impact implementation and delivery of evidence-based complex interventions. This is particularly evident when service delivery requires a high level of skill from therapists [11,38]. Investigation of the impact of therapist experience on therapy outcomes is therefore warranted. Further, while evidence is growing about health outcomes from implementation interventions across various settings and health professional groups [11,39], there is a paucity of data on their cost-effectiveness to inform whether the investment of resources justifies the additional benefits that might be achieved. Therefore, this study will also investigate cost-effectiveness of the intervention.

We have created a partnership of survivors of stroke, clinicians, researchers, healthcare organizations, and policy makers to (i) increase access to evidence-based SENSe therapy delivered by therapists via a network of clinical practice settings and specialist SENSe therapy centers, and (ii) improve outcomes for survivors of stroke with somatosensory impairment of the arm/hand. The partnership is supported with a National Health and Medical Research Council Partnership grant from Australia (GNT 1134495), which has allowed us to create a centralized knowledge-translation hub and four specialist therapy centers.

Two complementary studies, SENSe Implement [12] and SENSe CONNECT (ACTRN12618001389291), are being undertaken to address the identified gap and achieve our overall aims. Together, the studies will permit investigation across different modes of delivery and skill levels of therapists and will involve approximately 100 therapists and 250 stroke survivors. The first study, SENSe Implement [12] (ACTRN12615000933550), focuses on testing the effectiveness of our knowledge-transfer intervention to change clinician behavior in existing rehabilitation services. Specifically, the aim is to determine whether evidence-based knowledge-translation strategies change the practice of occupational therapists and physiotherapists in the assessment and treatment of sensory loss of the upper limb after stroke to improve patient outcomes. This study is being conducted as a pragmatic, before–after study involving eight Australian healthcare networks and existing sub-acute and community rehabilitation services (see [12] for further details).

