SENSe therapists will not be blinded due to pragmatic reasons. It is planned that each therapist will deliver SENSe therapy to up to 12 stroke survivors. A secondary analysis will permit investigation of the association between stroke survivor outcomes achieved and the therapist’s amount of experience in delivering SENSe therapy. The study is approved by Austin Human Research Ethics Committee (HREC/18/Austin/153), and all experiments will be performed in accordance with the Declaration of Helsinki. Site-specific ethics approvals were also obtained. All participants will give voluntary informed consent.

Sample size: Stroke survivors—The SENSe CONNECT study design requires a within-subject, repeated measures analysis. The within-group analysis from the original SENSe randomized controlled trial (RCT) revealed a Cohen d of 0.366 for the somatosensory function outcome (repeated measures, small group *n* = 22/50; [34]). To achieve a within-group effect of d = 0.366 for a power of 0.8, a minimum sample of *n* = 61 is required. In the current study, the proposed sample size of *n* = 72 to 192 (i.e., 18 to 48 deliveries at each of the 4 centers) achieves this minimum and allows for dropout or poor recruitment. Assuming the variability in changes found in the SENSe RCT is replicated in the delivery of SENSe therapy, a maximum sample size of *n* = 192 will have a high degree of precision for estimating the effect size obtained within the SENSe therapy centers. The larger sample size will also facilitate generalizability of effect estimates to the broader target population of survivors of stroke living in the community. Therapists—At each specialist SENSe therapy center, it is planned that 3 or 4 therapists will each deliver SENSe therapy to 6 to 12 stroke survivors (i.e., 18 to 48 deliveries at each site; 72 to 192 across sites). A sample of 12 to 16 therapists was chosen to maximize replication across upskilled therapists while exploring the association between the amount of experience in delivery of SENSe therapy and therapy outcomes.

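### The primary confidence interval and sample size take no account of therapist clustering, so the interval is somewhat too narrow if therapists differ

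*Protocol article*

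**What the plan says.** Section 2.8 (Effect of SENSe therapy) sets the primary estimate as "the mean within-person difference between the two trends and the associated 95% confidence intervals". For the interval, depending on a check of normality, "either a t-distribution or a bootstrapping method will be used to obtain the confidence interval". The only grouping factor named is center: "The analysis design will include the SENSe therapy center as a variable, to evaluate its potential systematic effect".

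Section 2.1.2 (Sample size) takes a within-group effect from the earlier SENSe RCT, which "revealed a Cohen d of 0.366 for the somatosensory function outcome", and concludes that "for a power of 0.8, a minimum sample of *n* = 61 is required". The planned range is 72 to 192. The same paragraph states that at each center 3 or 4 "therapists will each deliver SENSe therapy to 6 to 12 stroke survivors", giving 12 to 16 therapists in all. No design effect or ICC appears.

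The article expects that the therapist may matter. The Introduction says: "Skill and experience of the therapist may impact implementation and delivery of evidence-based complex interventions". Section 2.2 collects therapist demographics in order to relate them to survivor outcomes. The limitations paragraph of the Discussion says that therapist characteristics are not controlled for, only monitored and explored. Hierarchical modelling by therapist appears in section 2.8 only for the experience question.

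**The concern.** All participants treated by one therapist share whatever that therapist adds to or takes from the SENSe-phase change. If therapists differ, their participants' results are correlated, and a standard error that counts each participant as an independent unit is too small. Therapists are nested within centers, so a center term removes differences between centers but leaves differences between therapists in the same center.

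Two planned conclusions depend on the width of this interval: whether SENSe therapy outperforms usual care, and how far the estimates overlap with those of the benchmark RCT. The Discussion also wants results that generalise across a range of therapists, so variation between therapists belongs in the interval. The effect grows with caseload, so it is largest at the maximum of 192, for which section 2.1.2 claims a high degree of precision.

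**Working it through.** **Inputs.** From section 2.1.2: d = 0.366, power 0.80, minimum n = 61, 12–16 therapists, 6–12 participants each, total 72–192. Two-sided 5% is assumed, to match the 95% interval. The therapist ICC is not in the document; 0.02, 0.05 and 0.10 on the SENSe-phase gain (A3 − A2) are assumed.

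**1. The plan's own figure.** A paired t-test with d = 0.366 and two-sided 5% needs n = 61 (power 0.803). The normal approximation, ((1.96 + 0.842)/0.366)² = 58.6, gives 59. A one-sided t-test gives 48. So 61 reproduces exactly, with independent participants and no design effect.

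**2. From the gain to the phase difference.** The primary quantity compares two changes, (A3 − A2) − (A2 − A1) = A3 − 2A2 + A1. With equal, independent visit errors of variance σ²:
- error variance of the gain: 2σ²
- error variance of the phase difference: (1 + 4 + 1)σ² = 6σ², three times as large.

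The study therapist acts only in the SENSe phase, so the therapist variance is the same in both. If ρ is the ICC of the gain, the ICC of the phase difference is ρ / (ρ + 3(1 − ρ)):
- 0.02 / 2.96 = 0.007
- 0.05 / 2.90 = 0.017
- 0.10 / 2.80 = 0.036

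**3. Design effect.** DE = 1 + (m − 1) × ICC. The interval should be wider by √DE, and the effective sample is N/DE. A rough false-positive rate for the nominal 5% test is 2 × (1 − Φ(1.96/√DE)).

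Phase difference (the primary quantity):

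| ICC of gain | Therapists × participants | DE | √DE | Effective n | False positives |
|---|---|---|---|---|---|
| 0.02 | 12 × 6 | 1.03 | 1.02 | 69.6 | 5.4% |
| 0.05 | 12 × 6 | 1.09 | 1.04 | 66.3 | 6.0% |
| 0.10 | 12 × 6 | 1.18 | 1.09 | 61.1 | 7.1% |
| 0.02 | 16 × 12 | 1.07 | 1.04 | 178.7 | 5.9% |
| 0.05 | 16 × 12 | 1.19 | 1.09 | 161.4 | 7.2% |
| 0.10 | 16 × 12 | 1.39 | 1.18 | 137.8 | 9.7% |

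Simulation of the phase difference agrees: about 5.3–7.3% for 12 × 6 and 5.9–10.1% for 16 × 12.

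**4. The simple pre–post gain.** This is relevant to the secondary outcomes, which are evaluated pre–post. Here the ICC is not diluted. DE is 1.10–1.50 with 6 per therapist and 1.22–2.10 with 12. At ICC 0.10 the false-positive rate is about 10–11% for 12 × 6 and 17–18% for 16 × 12.

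**5. Does center help?** In simulation of the gain at ICC 0.10, coverage of the nominal 95% interval was 89.5% without center and 89.0% with center as a fixed effect at N = 72. At N = 192 it was 82.7% and 82.4%. An interval built on therapist means covered about 95% in every setting.

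**6. Sample size and precision.** At N = 72, the top of the assumed range leaves 61.1 effective participants for the phase difference. That is the plan's minimum with nothing left for dropout. If d = 0.366 is read as the effect on the gain, ICC 0.05 already gives 72/1.25 = 57.6, below 61. At N = 192 the half-width of 0.142 SD becomes 0.142 × 1.18 = 0.168 SD for the phase difference at the top of the range.

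**The case against.** The strongest reply is that no ICC is given, so the size rests on assumption, and that the phase difference dilutes any therapist effect. Both stand. At the low end the interval is only 2–4% too narrow. Credentialing, fidelity feedback and the 80% criterion are also meant to keep therapists alike.

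A second reply is that the article is condensed and names no resampling unit. A bootstrap over therapists would satisfy its wording, and the detail may sit in an unseen analysis plan. This stands in part: independence is inferred, not written. But the article does name the interval method and one grouping variable, and the n = 61 calculation assumes independence. Together these do not fit the stated design.

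Three stronger readings are tempting, and the documents do not support them.

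- A reader might infer that the study itself hypothesises differences between therapists. Aim 4 and the experience hypothesis in section 2.8 concern a trend over a therapist's successive cases. With equal caseloads, a learning curve common to all therapists creates no between-therapist variance: in simulation with a 0.5 SD rise from first to last case, the ordinary t-test rejected 4.7% of the time. Unequal caseloads could create some differences. The support lies instead in the Introduction, section 2.2 and the limitations paragraph, which allow for therapist effects without asserting a size.
- A reader might take the 17–18% false-positive rate as the figure for the primary analysis. It belongs to the simple gain, not to the difference between phases.
- A reader might infer that participants who miss a visit are dropped. The article does not say so.

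**Conclusion.** The point holds, at should-fix level. As stated, the primary interval has no therapist term and the sample size no design effect, so for any positive therapist variance in the SENSe phase the interval is too narrow. Center does not repair this.

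The likely size is modest: a correct interval about 2–9% wider at 12 × 6 and 4–18% wider at 16 × 12, with false-positive rates of about 5–7% and 6–10%. These figures rest on an assumed ICC of 0.02–0.10 for the gain, equal and independent visit errors, and equal caseloads. The direction does not depend on the assumed value; the size does.

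**What to change.** In section 2.8, state that the primary model includes a therapist random effect on the SENSe-phase change, with center kept in the model and Satterthwaite or Kenward–Roger degrees of freedom. If a bootstrap is used, state that therapists are resampled, not individual participants. In section 2.1.2, restate the minimum sample and the precision claim with an assumed therapist ICC, its range and the resulting design effect.

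No new data are needed: the planned experience analysis already requires each case to be linked to its therapist. The cost is a somewhat wider interval and fewer degrees of freedom. In the extreme case of a test on therapist means with 11 degrees of freedom, N = 72 and no therapist variance at all, power at d = 0.366 falls from 0.865 to 0.807. That is a reason to state the assumption before the data are analysed.
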